### Planned Analyses

For the primary outcome, the primary analysis will be an intention to treat analysis, with a *p*-value of <0.05 from a one-tailed chi square test of proportions considered statistically significant. The secondary analysis will be a per protocol analysis, excluding intervention group participants who did not attend at least three of the four intervention sessions. Secondary outcomes will be examined using chi square tests (for categorical variables), independent samples t-tests (for continuous variables) and discrete time survival analysis (for time to relapse).

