## Methods

### Study Design

The study is a randomised controlled trial comparing two groups of soon-to-be released male prisoners. Three hundred sentenced prisoners will be recruited from four correctional centres in Queensland. Intervention group participants will take part in four group sessions of CBT and MI encouraging smoking abstinence post release, in the 4 to 6 weeks prior to release from prison. The comparison group will receive usual care plus a pamphlet encouraging smoking abstinence and a brief verbal explanation of the pamphlet at baseline. After individual baseline screening interviews assessing smoking history and future smoking intentions, participants will be randomised 1:1 to the intervention or comparison group. Once participants are released from custody, parole officers will record their self-reported smoking status at every appointment, for a maximum of 3 months. The primary outcome is point-prevalence of tobacco smoking abstinence at 1 month post-release. This study has been approved by the Griffith University Human Research Ethics Committee and by the Queensland Corrective Services (QCS) Research Committee. The trial is registered with the Australian New Zealand Clinical Trials Registry (ACTRN12616000314426) (Fig. 1).

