### Sample size calculation

Sample size calculations were informed by the work of Clarke et al. (2013) who, based on a comprehensive review of the literature, conservatively estimated abstinence rates of 23% for the intervention group and 14% for the control group. With alpha of .05 one-tailed and a power level of at least .80, these estimates result in a desired sample size of 292, which we have rounded up to 300 participants. These estimates are considered conservative for two reasons. First, whereas participants in the study by Clarke et al. (2013) did not receive any cessation support from prison authorities, prisoners in Queensland receive a week’s supply of free nicotine patches upon incarceration, associated with long-term smoking abstinence (Stead et al., 2012; Wu et al. 2006). Second, the observed intervention effect in the study by Clarke et al. (2013) was larger than expected (25% vs. 7% at 3 weeks), and the intervention in this trial is an enhanced version of the WISE intervention.

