### Randomisation

After baseline assessment, each participant will be randomised 1:1 to the intervention or comparison group. Randomisation will be stratified by prison. The number of participants in each group per prison will reflect the sample distribution across the four prisons. Randomisation will also be stratified by intention to quit, given evidence (Thibodeau et al. 2010) that prisoners who have an intention to quit are more likely to remain abstinent post-release. The randomisation list will be divided into randomly permuted blocks of size 4, 6, or 8. Within each block, an equal number of intervention and comparison conditions will be assigned. Use of random permuted blocks ensures balance during assignment and helps to prevent participants from guessing which condition they have been assigned to (Beller et al. 2002). At this stage, the number of prisoners who intend to remain abstinent from smoking after release is unknown.

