The current study aims to investigate the effectiveness of a similar intervention in a different setting: four prisons in Queensland, Australia. There are four other noteworthy differences between this study and Clarke et al. (2013). In the WISE intervention, participants received six sessions of the intervention session; the sessions were delivered individually; comparison group participants watched health-related films; and participants had never been offered any form of NRT while incarcerated. In the proposed study, participants will receive four weekly group intervention sessions as opposed to six, which we believe will be equally effective and may reduce participant dropout; the intervention will be delivered in a group format, which is not only more efficient (and thus more likely to be supported by prison officials), but also an enhancement given evidence that group-based interventions are more effective for smoking cessation when compared to individual sessions (Stead & Lancaster, 2005); comparison group participants will receive a pamphlet and brief verbal intervention focused on smoking cessation, instead of watching a more generic health-related film; and finally, unlike their American counterparts, Queensland prisoners are offered 1 week of free NRT upon incarceration. As NRT use is linked to improved long-term smoking cessation (Wu et al., 2006), and evidence shows equal effectiveness for short- and long-term NRT treatment (Stead et al., 2012), we anticipate higher rates of tobacco smoking abstinence post-release compared to the WISE study.

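### The primary success rule is a one-tailed chi-square test at 5% with no stated direction or justification; its error rate and its ability to show harm depend on how it is read

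*Protocol article*

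**What the plan says.** Planned Analyses in the protocol article gives one decision rule for the primary outcome, in the intention-to-treat population: a p-value below 0.05 "from a one-tailed chi square test of proportions considered statistically significant". No direction is named, no reason is given for using one tail, and the article does not explain how a one-tailed p-value is taken from a chi-square statistic.

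The Sample size calculation section plans on the same basis: "With alpha of .05 one-tailed and a power level of at least .80", with assumed "abstinence rates of 23% for the intervention group and 14% for the control group". It concludes that "these estimates result in a desired sample size of 292, which we have rounded up to 300 participants". Study Design gives the same total, and under Randomisation "each participant will be randomised 1:1 to the intervention or comparison group", so there are 150 men per arm.

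The Discussion lists changes from the earlier US trial. Of the cut from six sessions to four it says "which we believe will be equally effective and may reduce participant dropout". Group delivery is presented there as an improvement supported by published evidence. The comparison arm receives a cessation pamphlet with a short explanation, where the earlier trial showed general health films.

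**The concern.** A one-tailed test needs a reason why a result in the other direction is impossible or of no interest. The article gives grounds to expect benefit, but none to rule out the opposite. The number of sessions has been reduced on the authors' belief that this does no harm to efficacy, and the comparator is itself aimed at cessation.

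The wording is also incomplete. The Pearson chi-square is the square of a z statistic, so the sign is lost. Two analysts could apply the sentence differently. One would halve the usual p-value and require the intervention arm to be better (critical value 2.71). The other would use the ordinary upper tail of the chi-square distribution (critical value 3.84).

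At stake is how a borderline or adverse result is reported. On the directional reading, a trial could be declared positive while a conventional two-sided 95% interval includes no effect, and a clear deficit in the intervention arm would have no formal expression.

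**Working it through.** **Inputs.** From the article: 23% and 14% abstinent, 300 men, 1:1 allocation (150 per arm), alpha 0.05 one-tailed, power at least 0.80. Assumptions made here: a pooled z test without continuity correction, and for the worked example 21/150 (14%) abstinent in the comparison arm. The 7% versus 14% harm scenario is an illustration and is not in the article.

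**1. The plan's own figure.** Per arm, n = [z_α √(2p̄(1−p̄)) + z_β √(p₁(1−p₁)+p₂(1−p₂))]² / (p₁−p₂)², with p̄ = 0.185.
- One-tailed: [1.645 × 0.549 + 0.842 × 0.545]² / 0.09² = (0.903 + 0.459)² / 0.0081 ≈ 229.1, so 230 per arm and 460 in total.
- Two-sided: (1.076 + 0.459)² / 0.0081 ≈ 291.0, so 292 per arm and 584 in total.

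The stated total of 292 is not reproduced. It equals the per-arm number for a two-sided 5% test. Unpooled, arcsine and continuity-corrected versions do not give 292 in total either.

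**2. Power with 150 per arm.** Power = Φ{[0.09 √150 − z_α × 0.549] / 0.545}.
- One-tailed: Φ(0.365) = 64.2%.
- Two-sided: Φ(0.048) = 51.9%.

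Exact enumeration of the two binomials gives 64.4% and 52.4%.

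**3. Two readings of the rule.** Critical values are 1.645² = 2.71 and 1.960² = 3.84. Exact enumeration at 150 per arm gives:

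| | Directional, z > 1.645 | Upper-tail chi-square > 3.84 |
|---|---|---|
| False benefit, 14% in both arms | 5.02% | 2.46% |
| Range over common rates of 7% to 23% | 4.96% to 5.04% | 2.35% to 2.52% |
| Can a worse intervention arm be declared worse? | No | Yes |
| Harm shown if 7% vs 14% | 0% | 51% |
| Benefit shown if 23% vs 14% | 64.4% | 52.4% |

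At the design rates the readings disagree in about 64.4 − 52.4 = 12% of trials. This is simply the power difference between the two thresholds.

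**4. Borderline results against 21/150.** z = (p₁−p₂) / √[2p̄(1−p̄)/150]. The interval is the difference ± 1.96 √[p₁(1−p₁)/150 + p₂(1−p₂)/150].

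| Intervention | z | Chi-square | One-sided p | Two-sided p | Difference, points (95% interval) |
|---|---|---|---|---|---|
| 32/150 | 1.67 | 2.77 | 0.048 | 0.096 | +7.3 (−1.3 to +15.9) |
| 33/150 | 1.80 | 3.25 | 0.036 | 0.071 | +8.0 (−0.6 to +16.6) |
| 34/150 | 1.94 | 3.76 | 0.026 | 0.052 | +8.7 (−0.04 to +17.4) |
| 35/150 | 2.07 | 4.30 | 0.019 | 0.038 | +9.3 (+0.6 to +18.1) |

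The directional rule first declares success at 32, the upper-tail rule at 35. Results of 32, 33 and 34 are successes under the first reading only.

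**The case against.** The strongest defence is that the rule was fixed in advance and is the same in planning and analysis. A one-tailed 5% test has a 5% error rate in its own direction by definition, and 2.5% is a convention that the article never adopts. The aim is directional and the planning rates put the intervention arm higher, so the directional reading is much the more natural one; on the other reading the word one-tailed would add nothing. All of this stands. The choice is unjustified, but it is not a contradiction in the text, and the ambiguity is one of loose wording.

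Some stronger readings are tempting and should not be drawn:
- A reader might infer that the 5% rate, the inability to show harm and the double meaning all apply at once. They do not: the first two belong to the directional reading, and under the upper-tail reading neither applies.
- A reader might infer that the authors merely believe the whole modified intervention works. The statement of belief covers only the cut to four sessions. For group delivery they cite evidence, and they also cite favourable results from the earlier trial.
- A reader might infer that no confidence interval will be reported. The article is condensed and does not exclude one; a fuller plan may contain it.
- A reader might argue that unblinded self-report calls for a stricter alpha. A stricter threshold does not remove that bias, and the article already acknowledges both limitations.

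The defence also rightly notes that a two-sided threshold is not free, because it lowers power in a trial that already falls short of its stated power.

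**Conclusion.** The concern holds in a conditional form. The only success criterion stated for the primary outcome is one-tailed, has no stated direction or justification, and is attached to a statistic without a sign. On the directional reading that the sample size section favours, false benefit is about 5.0% rather than about 2.5%, an adverse result can only be called not significant, and 32 to 34 abstinent of 150 against 21 of 150 would count as success with a 95% interval that includes zero. On the upper-tail reading, false benefit is about 2.5% and harm can be declared.

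These figures assume 150 analysed per arm, with losses counted as non-abstinent as the article states, and an uncorrected pooled test. The article does not show that a two-sided claim threshold is obligatory; that is a recommended trade-off. Under either rule the stated power of at least 80% is not reached with 300 men at the planning rates. The point merits a change to the stated rule, but it does not by itself invalidate the design.

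**What to change.** 1. Replace the sentence in Planned Analyses with a test that has one meaning: the signed z statistic for the difference in 1-month abstinence (intervention minus comparison), with a single stated critical value.
2. Report that difference with a two-sided 95% confidence interval, and interpret it in both directions, so that a borderline benefit or a deficit is described as such.
3. Preferably base the claim on a two-sided 5% test (|z| above 1.96, chi-square above 3.84). If one tail is kept, give the reason, fix the direction, and show the p-value beside the two-sided interval.
4. Restate the power in the Sample size calculation section to match the rule chosen: about 64% one-tailed or about 52% two-sided with 300 men at 23% versus 14%. Reaching 80% would take 460 or 584 men in total, respectively.

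Items 1 and 2 cost a few sentences and no data. Item 3 costs about 12 percentage points of power at the present size. Item 4 is needed whichever rule is chosen.

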### Groups and intervention

Intervention group participants will receive four weekly group sessions of the intervention in the 4 weeks prior to their release. They will be assigned to a group depending on their release date, ensuring that all members of each group are due for release at a similar time. Each group will consist of between four and six participants. Each intervention session will be approximately 40–60 min in duration, and will be arranged at dates and times that are convenient to the prisoners and prison staff.

Consistent with the WISE study (Clarke et al., 2013), sessions one and four will be based on principles of MI, and sessions two and three on CBT. MI sessions will focus on aiding the development of self-efficacy and personal choice, and on addressing group members’ ambivalence towards remaining abstinent from smoking post-release. The CBT sessions will teach participants to recognise specific environmental and event triggers to smoking and identify behavioural and coping strategies in response to these triggers. The intervention session plan is based on the successful WISE intervention delivered by Clarke et al. (2013) and has been adapted based on recommendations by a clinical psychologist with extensive experience in Australian correctional settings. Sessions will be delivered by the primary researcher, who has a background in psychology and counselling and has received further training in CBT and MI techniques.

Prisoners in the comparison group will receive a pamphlet at the end of the baseline assessment, as well as a brief (1 to 2 min) verbal explanation of the pamphlet. The pamphlet highlights the advantages of staying abstinent from smoking post-release, and provides tips for doing so.

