### Outcomes

The primary outcome of this study is point-prevalence tobacco abstinence at 1 month post-release, measured by self-report. Secondary outcomes include number of weeks to first cigarette after release, amount of tobacco consumed in the event of relapse, and point-prevalence of tobacco abstinence at 3 months post-release. Participants lost to follow-up will be considered non-abstinent—the most conservative assumption.

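### The secondary per-protocol analysis drops low attenders from the intervention arm only, so it is not a randomised comparison and can overstate benefit

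*Protocol article*

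**What the plan says.** Planned Analyses states that for the primary outcome "the primary analysis will be an intention to treat analysis", judged at 0.05 by a "one-tailed chi square test of proportions considered statistically significant". It then names as the secondary analysis a "per protocol analysis, excluding intervention group participants who did not attend at least three of the four intervention sessions". The rule names intervention participants only, and the section mentions no adjustment for the selection.

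Three other places bear on this:
- Groups and intervention: "Prisoners in the comparison group will receive a pamphlet at the end of the baseline assessment", with an explanation of one to two minutes. No attendance can be recorded in that arm.
- Randomisation: stratification by intention to quit is justified by evidence that "prisoners who have an intention to quit are more likely to remain abstinent post-release".
- Outcomes: "Participants lost to follow-up will be considered non-abstinent".

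**The concern.** Whether a man attends three sessions is settled after allocation. Some men in the comparison arm would also have attended fewer than three sessions had they been offered them. They cannot be identified, so they stay in. Their counterparts in the intervention arm are removed. If such men relapse more often, the retained intervention group has a better prognosis than the arm it is compared with, whether or not the sessions work.

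The article holds that baseline motivation is prognostic, and sitting through weekly sessions on staying abstinent plausibly reflects motivation. Counting losses as non-abstinent can add to the imbalance. If low attenders are also lost more often, their imputed failures leave the intervention arm, while the matching failures remain in the comparison arm.

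This is the named secondary analysis of the primary outcome. The risk is that a non-significant intention-to-treat result is reported beside a significant per-protocol result, and the second is taken as evidence of efficacy in men who engaged.

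**Working it through.** The article gives no figure for the per-protocol analysis, so there is none to reproduce. The check asks how often the per-protocol test rejects when the intervention does nothing.

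**Inputs from the article.** 300 men randomised 1:1, so 150 per arm; one-tailed chi-square test at 0.05; exclusion of intervention men with fewer than three of four sessions; no exclusion in the comparison arm.

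**Assumed inputs (not in the article).** *a* = proportion attending at least three sessions; *pA* = abstinence in the attending type; *pL* = abstinence in the low-attending type. Randomisation gives both arms the same mix of types.

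**Formulas under no effect.**
- Comparison arm: *pC* = *a*·*pA* + (1 − *a*)·*pL*
- Per-protocol intervention group: *pA*, with *n* = 150*a*
- Spurious difference: *pA* − *pC* = (1 − *a*)(*pA* − *pL*)
- Reject if z = (x/n − y/150) / √[p̄(1 − p̄)(1/n + 1/150)] > 1.645, summed exactly over both binomial distributions

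**Worked case (70% attending, 20% vs 8%).** *pC* = 0.7 × 0.20 + 0.3 × 0.08 = 0.164. Spurious difference = 0.3 × 0.12 = 3.6 points. n = 105. Hand check by normal approximation:
- pooled rate = (21 + 24.6)/255 = 0.179
- null SE = 0.0488, so the critical difference is 1.645 × 0.0488 = 0.080
- SE under the assumed rates = 0.0494
- (0.036 − 0.080)/0.0494 ≈ −0.9, a rejection rate of about 18%

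Exact enumeration gives 18.4%.

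**Range of cases (exact, no true effect).**

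| Attending ≥3 | *pA* vs *pL* | *n* kept | *pC* | Spurious difference | Per-protocol rejection |
|---|---|---|---|---|---|
| 70% | 10.8% vs 21.5% (low attenders do better) | 105 | 14.0% | −3.2 points | 0.8% |
| 70% | 14% vs 14% (not prognostic) | 105 | 14.0% | 0 | 5.3% |
| 90% | 20% vs 10% | 135 | 19.0% | +1.0 | 7.5% |
| 80% | 20% vs 8% | 120 | 17.6% | +2.4 | 13.2% |
| 70% | 20% vs 8% | 105 | 16.4% | +3.6 | 18.4% |
| 60% | 20% vs 5% | 90 | 14.0% | +6.0 | 33.6% |

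The intention-to-treat test rejects about 5.0% of the time in every row. For scale, the planned difference is 23% − 14% = 9 points, so 3.6 points is 40% of it.

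**How often the two analyses disagree.** Simulation of a million trials per case gives the frequency of a non-significant intention-to-treat result beside a significant per-protocol result, again with no true effect. It is about 2% to 3% with 90% attending and a twofold abstinence ratio, about 14% in the 70% case and about 29% in the 60% case.

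**Complier estimate in the same model.** The intention-to-treat difference has expectation 0, and 0/*a* = 0, so the spurious difference disappears. With a real 9-point intention-to-treat difference and 70% attending, the estimate is 9/0.7 = 12.9 points. Its standard error is about 1/0.7 = 1.43 times that of the intention-to-treat difference.

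**The case against.** Four points can fairly be made for the plan.

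1. **Size and direction are not established.** A reader might infer that the rule is bound to produce a false benefit. The article does not support that. It gives no attendance rate and no association between attendance and abstinence. Its remark on prognosis concerns baseline intention to quit, not session attendance. Men in custody may miss sessions for institutional reasons, since sessions are fitted around both prisoners and staff. If absence is unrelated to prognosis there is no bias, and if low attenders did better the bias reverses. This stands, and it is why the claim is that the analysis can overstate benefit.

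2. **Disagreement between the analyses is not the expected outcome.** A reader might infer that a null primary result beside a significant per-protocol one is likely. In the no-effect cases with a prognostic advantage for attenders, it occurs in about 2% to 29% of trials. It is a realistic possibility, no more.

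3. **The main conclusion does not rest on this analysis.** Intention to treat is primary, the three-session cut-off is fixed in advance, and nothing in the article says a per-protocol result would support an efficacy claim. This stands in full and limits the weight of the point. Prespecification does not restore comparability, though.

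4. **The complier estimate has its own assumption.** It treats one or two sessions as having no effect, yet session one is active motivational interviewing. If partial attendance helps, the estimate overstates the effect of attending three or more. This stands and has to be handled in the fix.

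It might also be said that such detail belongs in an unseen analysis plan. That does not answer the point, because the article itself defines the exclusion rule.

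**Conclusion.** The point holds as a defect in a secondary analysis. The stated rule conditions on post-randomisation behaviour in one arm only. It yields a valid comparison only if attendance is unrelated to prognosis, and the article's own view of motivation makes that hard to assume. That the retained men are compared with the whole comparison arm is inferred from the absence of any exclusion there.

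Under no true effect with 150 per arm, the false-positive rate runs from about 5% when attendance is not prognostic, through 7.5% and 18%, to 34% in the least favourable case worked. It falls below 5% if low attenders do better. These figures rest on assumed attendance and abstinence rates and are not predictions for this trial. The intention-to-treat analysis keeps its 5% level throughout, so nothing here calls the primary result into question.

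**What to change.** Replace the per-protocol test with a complier average causal effect for attending at least three sessions, using randomised allocation as the instrument:

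- Estimate: the intention-to-treat risk difference at 1 month divided by the proportion of the intervention arm attending at least three sessions, with a bootstrap or two-stage confidence interval.
- State the assumption that one or two sessions have no effect, and say that it is doubtful because the first session is already active treatment.
- Add a sensitivity analysis that counts any attendance as treated, with the proportion attending at least one session as the divisor.
- If as-attended abstinence rates are shown, label them descriptive, give no p-value, and do not use them to support an efficacy claim.

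The cost is a change of analysis wording, a wider confidence interval (by a factor of about 1.43 relative to intention to treat if 70% attend) and an assumption that must be declared. Session attendance is already needed for the planned rule, so no new data are required.

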### Measures

The baseline assessment will be administered individually to all participants and will take 15–20 min to complete. It measures participants’ smoking history, overall health status, drug use history, nicotine dependence (using the Fagerström Test for Nicotine Dependence; Fagerstrom & Schneider, 1989), and post-release smoking intentions and desires. The assessment was designed by the authors and informed by previous research (e.g. Clarke et al., 2011, 2013; Richmond et al. 2013a, 2013b).

Once participants have been released from prison, parole officers will assess participants’ self-reported smoking status at each appointment, using four questions: 1) Have you smoked since release? 2) If yes, how many weeks ago did you first smoke? 3) Are you currently smoking? 4) If yes, how many cigarettes do you smoke on average per day? In this way, absolute smoking status, duration of smoking abstinence, and intensity of the relapse (e.g., quantity of cigarettes smoked per day) can be measured. These questions also account for situations where a participant may have had a ‘lapse rather than a relapse’ (e.g., temporarily resumed smoking, then returned to abstinence).

Most parolees meet with their parole officers weekly, but some meet fortnightly or monthly. Parole officers will assess parolees’ smoking status at every meeting, but all participants will be assessed at 1 month post-release (the primary endpoint). Parole officers will continue to ask these four questions at each meeting with the participant for up to 3 months post-release. The rationale for a 3-month end point is that the majority of smoking relapses occur within the first 3 months post-release (Ockene et al., 2000). Clarke et al. (2013) also support this relatively brief follow-up period due to the high relapse rates immediately after release. Although restricting the study to parolees may have implications for generalisability, this is offset by an expected low rate of attrition, since most parolees are expected to attend most of their parole meetings.

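### Cigarettes per day after relapse is compared by an unadjusted t-test, although a dependence score and smoking history are collected from every man before randomisation

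*Protocol article*

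**What the plan says.** The Outcomes section lists three secondary outcomes: weeks to first cigarette, "amount of tobacco consumed in the event of relapse", and abstinence at 3 months. Planned Analyses assigns methods by type of variable: chi square tests for categorical outcomes, "independent samples t-tests (for continuous variables", and "discrete time survival analysis (for time to relapse". Abstinence at 3 months therefore goes to chi square and time to first cigarette to the survival model. That leaves the amount smoked as the listed outcome for the t-test.

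Under Measures, parole officers obtain the amount by asking current smokers only: "If yes, how many cigarettes do you smoke on average per day".

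The same section says: "The baseline assessment will be administered individually to all participants". Its content includes "smoking history, overall health status, drug use history, nicotine dependence", the last measured "using the Fagerström Test for Nicotine Dependence". Recruitment and inclusion criteria places randomisation at the end of this assessment, so these are genuine pre-randomisation covariates. Randomisation is stratified by prison and intention to quit, and by no measure of smoking intensity or dependence. The article describes no covariate-adjusted analysis.

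**The concern.** How dependent a man was, and how heavily he used to smoke, are natural predictors of how much he smokes if he relapses. A two-sample t-test has no place for a covariate, so any variation between men that these measures explain stays in the error term. Since the design does not balance the arms on dependence, a baseline difference among the men analysed also passes uncorrected into the estimated difference.

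What is at stake is the precision of one secondary comparison: a confidence interval possibly wider than the collected data require, and some lost power for an effect on smoking intensity. The protocol names the test, so this is a stated choice and not a detail left open.

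**Working it through.** **The plan's own figure.** There is none for this outcome. The only sample-size figure (292, rounded up to 300) concerns abstinence and is not tested here; only the 300 and the planning rates are used.

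**Inputs from the protocol article**
- 300 men randomised 1:1, so 150 per arm (Study Design, Randomisation).
- Abstinence 23% with intervention and 14% with comparison (Sample size calculation).
- Men lost to follow-up count as non-abstinent (Outcomes).

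**Assumptions**
- ρ, the within-arm correlation among relapsers between the baseline covariate and later cigarettes per day: 0.1 to 0.7. With two covariates, read ρ² as their joint R².
- A two-sided 5% test. The article fixes a one-tailed test for the primary outcome and states no sidedness for secondary outcomes.

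**Step 1: men available.** 150 × 0.77 = 115.5 and 150 × 0.86 = 129, together 244.5, or about 245. At the planning rates this is a ceiling, because men counted as non-abstinent through loss to follow-up have no cigarettes-per-day value.

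**Step 2: reference effect.** The effect detectable with 80% power by the unadjusted test is (1.960 + 0.842) × √(1/115.5 + 1/129) = 2.802 × 0.128 = 0.359 SD. The noncentral t distribution gives 0.361 SD.

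**Step 3: effect of adjustment.** Residual variance is multiplied by 1 − ρ², interval width by √(1 − ρ²), and effective sample size by 1/(1 − ρ²). Power at the reference effect is Φ(2.802/√(1 − ρ²) − 1.960). At ρ = 0.3, for example, 2.802/0.954 − 1.960 = 0.977, and Φ(0.977) = 0.836.

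| ρ (assumed) | Variance factor | Interval narrower by | Power, two-sided 5% | Equivalent extra men |
|---|---|---|---|---|
| 0.1 | 0.99 | 0.5% | 80.4% | 2 |
| 0.2 | 0.96 | 2.0% | 81.6% | 10 |
| 0.3 | 0.91 | 4.6% | 83.6% | 24 |
| 0.4 | 0.84 | 8.3% | 86.4% | 47 |
| 0.5 | 0.75 | 13.4% | 89.9% | 82 |
| 0.6 | 0.64 | 20.0% | 93.8% | 138 |
| 0.7 | 0.51 | 28.6% | 97.5% | 235 |

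The power column starts from 80% by construction and does not depend on the number of relapsers. Fewer relapsers raise the detectable effect and leave the relative gain unchanged. With a one-sided 5% test the reference effect is 0.319 SD, and power becomes 81.4%, 83.2% and 89.0% at ρ of 0.2, 0.3 and 0.5, much the same picture.

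**Step 4: simulation.** With 115 and 129 men, normal outcomes and 4,000 runs per value of ρ, adjusted power was 82.7%, 90.0% and 97.6% at ρ of 0.3, 0.5 and 0.7, in line with the formula. At ρ = 0 it was 79.2%, against 79.7% unadjusted, so a useless covariate costs almost nothing.

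**The case against.** The strongest reply is that nothing here is an error. An unadjusted t-test on a secondary outcome is a standard choice, the article covers the secondary outcomes in one sentence, and the trial is sized for abstinence alone. That stands: the point is about efficiency and carries little weight.

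The size of the gain is also undocumented. Below ρ of about 0.2 it is negligible, and it exceeds 5 percentage points only from roughly 0.4. The baseline is recalled after at least four weeks in a smoke-free prison, and the outcome is self-reported to a parole officer; both may weaken the correlation. This stands too, and it rules out any flat statement that precision is being lost by a known amount.

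A reader might infer that cigarettes per day before prison are on file as a ready covariate. The article says only that smoking history is taken. That it refers mainly to the time before custody is a fair inference from the eligibility criteria, but no numeric level is documented. The Fagerström test is the only named instrument, so it should be the main covariate.

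The weightiest objection is that the outcome exists only in men who relapse, a group formed after randomisation. If the intervention changes who relapses, baseline differences between the arms' relapsers reflect selection as well as chance. A reader might infer that adjustment repairs this. It does not: it reduces imbalance on what was measured and leaves the rest. That problem is more serious than lost precision, but it is separate and gives no reason to prefer the unadjusted test.

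**Conclusion.** The point holds as a modest one. The protocol fixes a test that cannot use relevant pre-randomisation measures collected from every man. With correlations of 0.2, 0.3 and 0.5, adjustment would remove about 4%, 9% and 25% of the residual variance and raise power from 80% to about 82%, 84% and 90%. These figures rest on an assumed correlation and an assumed two-sided 5% level. The count of about 245 relapsers is an upper figure at the planning rates.

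A reader might conclude that the t-test is invalid or that the trial's main finding is exposed. Neither follows. The test is legitimate but possibly inefficient, and the one-tailed chi square on abstinence at 1 month is untouched.

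**What to change.** In Planned Analyses, replace the t-test for cigarettes per day with a linear model of cigarettes per day on arm. Pre-specify the baseline Fagerström score as the covariate, and add baseline cigarettes per day if the smoking history records it. Use robust standard errors, since cigarette counts are likely to be skewed. Report the adjusted mean difference with its confidence interval, and describe it as conditional on relapse. Name the covariates before outcome data are seen, so that the choice adds no analyst discretion.

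State how missing baseline scores will be handled. The eligibility criteria do not require previous smoking, so a score may be absent because a man never smoked. Such men should be scored as zero dependence and not given an imputed mean.

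The cost is a few sentences of analysis wording and one or two degrees of freedom out of roughly 240. No new data, visits or participants are needed.
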